### Data collection

The following demographic data and previous medical history will be collected by a data collector preoperatively from the medical records: sex, age, height, weight, duration of diabetes, and the presence of any complications of diabetes.

Peripheral venous blood samples will be extracted at T1, T2, T3, and T4, and urine samples will be obtained on the morning of postoperative days 1 and 3. The samples will be sent immediately to the clinical laboratory in PUMCH and will be analyzed by the staff there. Blood samples will be centrifuged at room temperature to obtain serum. Serum CysC concentration will be determined by sandwich enzyme-linked immunosorbent assay (ELISA), and Cr will be measured using an enzymatic method. Urine samples will be analyzed by automated urine microscopy analysis. All the samples will be handled within one hour since their arrival at the laboratory. We do not plan to store the samples after the study.

During the surgery, in addition to the secondary outcomes, two data collectors will record the heart rate, ABP, SV, and SVV every 15 min. They will also record the amount of crystalloid and colloid infused, the amount of transfusions, and the estimated blood loss.

There is an anesthesiologist and a surgeon in charge of monitoring the adherence to the protocol. Any suspected nonadherence during participant recruitment, randomization, intervention, data collection, or outcome assessment will be recorded. Based on the intention-to-treat (ITT) principle, all the randomized participants will be analyzed, despite any nonadherence to the protocol.

Data will be collected in the paper-based case report form (CRF) and then entered into a digital database by two independent investigators. Each patient will be distinguished by a unique serial number, and his or her name will be concealed. The database will be secured by a password, which will be restricted to the Data Safety Monitoring Committee (DMC), which is composed of two anesthesiologists with more than 10 years of experience. They will check the completeness and accuracy of the data, and the auditing will be independent from that of the other investigators. The information recorded in medical charts and saved in monitors will be traced to correct and supplement the data. The database will be locked up after the entry of the last case. The allocation will not be unblinded until all data analysis is completed; thus, the data analyst will also be blinded.

### Sample size calculation and statistical analysis

A previous study [15] reported that the standard deviation of serum CysC level after laparoscopic procedures is 0.738 ± 0.186 mg/dl. For a CysC difference of 0.05 mg/dl to be considered clinically significant, a power analysis program (G* power 3.1) calculated that a total sample size of 582 patients is needed to achieve 90% power at the 5% significance level. Considering a 10% dropout rate, a total of 648 patients (162 per group) is necessary. Approximately 5000 patients are scheduled for elective major pelvic surgery in PUMCH every year, and approximately 15% of them have diabetes; thus, one year is estimated as necessary to achieve adequate participant enrollment.

We will first compare the two SPP groups with the two LPP groups and then compare the two deep-NMB groups with the two moderate-NMB groups. Finally, all four groups will be compared.

The baseline characteristics and intraoperative factors of the enrolled patients will be evaluated using descriptive analysis. Continuous variables will be summarized as the mean  ±  standard deviation (SD) or median (interquartile range, IQR) as appropriate, whereas categorial variables will be summarized as the number (percentage). The baseline characteristics will be compared between groups using the standardized difference, and a standardized difference < 0.2 will be considered an acceptable balance between groups. Unbalanced variables at baseline will be included in the ANOVA or mixed-effects model to adjust for the potential confounding effect.

Considering the multiple measures of CysC, Cr, surgical condition rating scale, and renal tissue oxygen saturation at different time points, the effect of intervention in the whole timeframe will be analyzed by a mixed-effects model. Other continuous variables will be compared by two-sided independent Student’s t tests or the Mann–Whitney U test, as appropriate. Categorical variables will be analyzed by a Chi-square test or Fisher’s exact test, as appropriate. The Bonferroni method will be used to correct the potential increase in the probability of a type I error when analyzing the differences between the four groups.

We will also investigate the interaction between pneumoperitoneum pressure and NMB on postoperative renal function. The difference in serum Cysc levels at T2 between the S + D and L + D groups will be compared with that between the S + M and L + M groups. If there is no significant difference, we will assume there is no interaction.

We will perform statistical analysis using R (version 3.4.4). Two-sided *P* values < 0.05 will be considered significant.

Based on ITT principle, we will analyze all the post-randomization cases, including the ones with missing data. The missing data of the repeatedly measured outcomes will be imputed using the “last observation carried forward” method, while the missing data of other outcomes will be imputed by baseline data. Sensitivity analysis will be performed to assess the bias that may be introduced due to nonadherence to protocol or missing data.

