### Outcome measures

The primary outcome is serum CysC level, which is a sensitive biomarker of renal injury, and this will be measured 30 min before pneumoperitoneum insufflation (T1), 30 min after pneumoperitoneum deflation (T2), 24 h postoperatively (T3), and 72 h postoperatively (T4). Among them, T1 will be the baseline. The mean difference of the serum CysC between groups will be used as the effect measure. We will compare the serum CysC between groups throughout T2, T3, and T4, using mixed-effect model which can provide an estimate for the overall effect in the whole timeframe.

The secondary outcomes include four indicators of renal function: (1) serum Cr level measured at T1, T2, T3, and T4; (2) intraoperative urine output; (3) the presence of erythrocytes in urinary sediment on postoperative days 1 and 3; and (4) renal tissue oxygen saturation measured every 15 min following pneumoperitoneum insufflation, and cerebral oxygen saturation will be used as an internal reference to adjust individualized differences. The other three secondary outcomes selected to evaluate surgical conditions are (1) surgical condition rating scale measured every 15 min starting from the introduction of the first trocar by five surgeons independently, (2) duration of surgery, and (3) the occurrence of bucking or body movement during the surgery. The details of the secondary outcomes are demonstrated in Table 3.

**Table 3 Tab3:** The secondary outcomes

Domain	Measurement	Metric	Aggregation	Time point
renal function	serum Cr level	difference between groups in the whole timeframe	mean	30 min before PP insufflation, 30 min after PP deflation, postoperative 24 h, and postoperative 72 h
renal function	intraoperative urine output	difference between groups	mean	NA
renal function	the presence of erythrocytes in urinary sediment	difference between groups	portion	postoperative day 1 and day 3
renal function	renal tissue oxygen saturation	difference between groups in the whole timeframe	mean	every 15 min since PP insufflation
surgical condition	surgical condition rating scale	difference between groups in the whole timeframe	median	every 15 min starting from the introduction of the first trocar
surgical condition	duration of surgery	difference between groups	mean	NA
surgical condition	the occurrence of bucking or body movement during surgery	difference between groups	portion	NA

*Abbreviations*: *NA* not applicable, *PP* pneumoperitoneum

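### Baseline cystatin C should always be in the primary model; as written, it enters only after an observed imbalance, which on a factorial margin happens in about 1–2% of randomizations

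*Protocol article*

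**What the plan says.** Outcome measures lists four CysC samples, T1 to T4, and then separates the first: "Among them, T1 will be the baseline". The primary comparison is made over T2, T3 and T4 by a mixed-effects model, so T1 is not a response.

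Sample size calculation and statistical analysis gives the covariate rule. Groups are compared at baseline by standardized difference; a value under 0.2 "will be considered an acceptable balance between groups". Then: "Unbalanced variables at baseline will be included in the ANOVA or mixed-effects model to adjust for the potential confounding effect". No sentence puts T1 CysC into the model whatever its balance, and none defines the outcome as change from baseline. The same section plans three sets of comparisons: pressure, neuromuscular block (NMB), and all four groups.

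For creatinine, the Table 3 entry is a mean difference over the whole timeframe, and its time points include the sample taken 30 min "before PP insufflation". The text does not repeat for creatinine that T1 is the baseline.

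**The concern.** The pre-insufflation value of the primary outcome is the obvious covariate for its later values. It is sampled by plan, and pneumoperitoneum pressure cannot have affected it. A rule that admits it only after an observed imbalance has three consequences.

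- In most trials the covariate stays out, and whatever precision it offers is lost.
- The model is chosen after looking at the data, and the three sets of comparisons may end up with different covariates.
- A chance gap just below the cut-off goes uncorrected, although the cut-off is wide relative to the small effect this trial targets.

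At stake are the width of the primary interval and the prespecification of the primary model.

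**Working it through.** **Inputs from the protocol.** Target difference 0.05 mg/dl ("For a CysC difference of 0.05 mg/dl to be considered clinically significant"); SD 0.186 mg/dl, a postoperative value ("the standard deviation of serum CysC level after laparoscopic procedures is 0.738 ± 0.186 mg/dl"); two-sided 5%, 90% power; 582 evaluable and 648 enrolled, so 291 or 324 per factorial margin and 145.5 or 162 per group; cut-off 0.2.

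**Assumptions, because the protocol gives no figure.** The T1 SD equals 0.186. The correlation ρ of T1 with each follow-up value is 0.3 to 0.8. For the mean of T2–T4, all four times have equal SDs and equal correlations (compound symmetry).

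**1. The plan's own figure.** n per margin = 2 × (1.960 + 1.282)² × 0.186² / 0.05² = 290.8, so 291, or 582 in total. This reproduces the stated number with no baseline adjustment. 582 / 0.90 = 647, rounded up to 648 for four equal groups.

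**2. How often the trigger fires for T1 CysC.** Under randomization the standardized difference is approximately N(0, 2/n), with n per side.

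| Comparison | SE = √(2/n) | P(absolute value ≥ 0.2) |
|---|---|---|
| 291 v 291 | 0.0829 | 1.6% |
| 324 v 324 | 0.0786 | 1.1% |
| 145.5 v 145.5 | 0.1172 | 8.8% |
| 162 v 162 | 0.1111 | 7.2% |

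By simulation, at least one of the six pairs among the four groups crosses 0.2 in 27% (162 per group) to 32% (145.5 per group) of trials.

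**3. What a gap at the cut-off would carry.** 0.2 × 0.186 = 0.037 mg/dl in the covariate, which is 74% of 0.05. The part passed into the unadjusted effect is ρ × 0.0372:

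- ρ = 0.5: 0.0186, 37% of target
- ρ = 0.7: 0.0260, 52%
- ρ = 0.8: 0.0298, 60%

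On a 291 v 291 margin such a gap lies 0.2 / 0.0829 = 2.4 standard errors from zero, hence the 1.6% above.

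**4. Precision forgone.** At a single time point, adjustment multiplies the variance by 1 − ρ². For the mean of three follow-ups, the variance factor goes from (1 + 2ρ)/3 to (1 + 2ρ)/3 − ρ².

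| ρ (assumed) | Variance removed, one time | Variance removed, mean of T2–T4 | Power at 582 for the mean: unadjusted → adjusted |
|---|---|---|---|
| 0.3 | 9% | 17% | 99.3% → 99.8% |
| 0.5 | 25% | 38% | 97.8% → 99.9% |
| 0.7 | 49% | 61% | 95.2% → >99.9% |
| 0.8 | 64% | 74% | 93.6% → >99.9% |

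More than half the variance is removed only if ρ exceeds about 0.71 (one time: ρ² > 0.5) or about 0.61 (mean of three: ρ² > (1 + 2ρ)/6).

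**The case against.** The strongest reply is that little is at risk. The unadjusted comparison is unbiased over randomization, and its standard error already allows for chance baseline gaps. The planned 582 does not rely on adjustment, and averaging three follow-ups gives power above 90% without it. All of this stands, and it limits the point to efficiency and prespecification.

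It can also be said that the model is practically fixed for the pressure and NMB contrasts, since the trigger fires for T1 CysC in only 1–2% of trials. That is fair for those two margins. It does not hold for the four-group comparison, where a crossing in some pair is quite likely.

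A third reply is that T1 CysC may not be among the screened variables: Data collection lists demographics and history, Table 1 is not shown, and an analysis plan might use T1 in another way. The uncertainty is real. But if T1 CysC is not screened, the stated rule never admits it at all, so neither reading of the article gives routine adjustment.

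Three stronger readings are tempting and are not supported.

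- A reader might take the 74% as bias in the treatment effect. It is a gap in the covariate at the very edge of tolerance; the part carried over is ρ times that, and the event is rare.
- A reader might infer that most of the available precision is thrown away. That needs ρ above about 0.61 to 0.71, and the protocol gives no ρ.
- A reader might infer from Table 3 that the creatinine effect is diluted by a quarter. That requires T1 to be a response under one common group effect across all four times. No sentence specifies such a model, the column can be read as a sampling schedule, and no power is stated for creatinine. This is an ambiguity to clear up, not a demonstrated error.

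**Conclusion.** The point holds as an avoidable inefficiency and a data-dependent choice of covariates. On the rule as written, T1 CysC would be left out of the pressure comparison in about 98–99% of randomizations, while the four-group comparison could well include it. The variance forgone is 9–64% at one time point or 17–74% for the mean of T2–T4, over assumed correlations of 0.3 to 0.8. In power for the mean this is a modest gain, about 0.5 to 6 points, because unadjusted power is already 94–99% under the same assumptions; the practical benefit is a narrower interval. These sizes rest on the assumed correlation, on a T1 SD equal to 0.186 for the gap in mg/dl, and on compound symmetry for the T2–T4 mean. The trigger probabilities need only randomization and the stated group sizes. Nothing here calls the sample size or the validity of the unadjusted test into question.

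**What to change.** Change the analysis section, before unblinding, along these lines:

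- CysC at T2, T3 and T4 is analysed in a mixed-effects model with pressure, NMB depth and time, and with T1 CysC as a covariate whatever its observed balance. The same covariate is used in the pressure, NMB and four-group comparisons.
- Creatinine is handled the same way, with T1 creatinine as covariate and T2–T4 as outcome. Table 3 should mark T1 as the baseline.
- Standardized differences are reported as description only and do not select covariates. Any further covariates are named in advance.

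The T1 blood sample is already planned for every patient, so the cost is wording: no added visits, samples or patients.

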### Participant selection

All patients scheduled for elective laparoscopic pelvic surgeries under general anesthesia will be screened for eligibility by an investigator who will not be involved in the process of randomization, intervention, data collection, or outcome assessment. Patients will be considered eligible if they meet the inclusion criteria and do not meet the exclusion criteria. Written informed consent will be obtained after evaluation.

The inclusion criteria are as follows:
Age 18–70 yearsAmerican Society of Anesthesiologist (ASA) Classification II-IIIDiagnosis of diabetes mellitusEstimated surgery duration > 3 h. The estimated surgery duration will be determined by the average duration of the same type of surgery by the same surgeon in the last year.

The exclusion criteria are as follows:
Not willing to participate in the study or unable to sign informed consentDiagnosis of any kidney diseases other than diabetic kidney diseasesSevere renal insufficiency defined as serum Cr > 2 times the upper limit of normal, urine output < 0.5 ml/kg/h, or estimated glomerular filtration rate (eGFR) < 60 ml/hSevere liver, lung or heart dysfunctionKnown or suspected neuromuscular diseaseUse of drugs that may affect neuromuscular block monitoringSevere diabetic neuropathy or any other peripheral neuropathyKnown or suspected allergy to general anestheticsFamily history of malignant hyperthermiaPrevious history of pelvic surgery

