### Randomization and blinding

After enrollment, just prior to the surgery, the patients will be randomized by a statistician without the knowledge of random allocation in a balanced manner to one of the four groups. The allocation sequence will be computer-generated using random block sizes and will be kept in an opaque sealed envelope. These assignment envelopes will only be opened by a nurse, who will set the pneumoperitoneum pressure, prepare the muscle relaxant, and monitor the depth of NMB. Therefore, participants, anesthesiologists, surgeons, and outcome assessors will all be blinded to the allocation throughout the trial.

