#### Surgical condition rating

A well-validated, 5-point scale, Leiden’s surgical condition rating scale (Table 2) [33], will be used. The laparoscopic pelvic surgeries for the enrolled patients will be performed by five surgeons. Before the study begins, they will be asked to watch the videos demonstrating examples of scales 1–5.

**Table 2 Tab2:** The surgical rating score [33]

Score	Impression	Description
1	Extremely poor conditions	The surgeon is unable to work because of coughing or because of the inability to obtain a visible laparoscopic field because of inadequate muscle relaxation. Additional neuromuscular blocking agents must be given.
2	Poor conditions	There is a visible laparoscopic field, but the surgeon is severely hampered by inadequate muscle relaxation with continuous muscle contractions, movements, or both with the hazard of tissue damage. Additional neuromuscular blocking agents must be given.
3	Acceptable conditions	There is a wide visible laparoscopic field but muscle contractions, movements, or both occur regularly causing some interference with the surgeon’s work. There is the need for additional neuromuscular blocking agents to prevent deterioration.
4	Good conditions	There is a wide laparoscopic working field with sporadic muscle contractions, movements, or both. There is no immediate need for additional neuromuscular blocking agents unless there is the fear of deterioration.
5	Optimal conditions	There is a wide visible laparoscopic working field without any movement or contractions. There is no need for additional neuromuscular blocking agents.

During the surgery, the surgeon will evaluate with the scale every 15 min starting from the introduction of the first trocar. At the same time, a 1-min video will be recorded by a camera connected to the endoscopic probe. The other four surgeons who will not perform this surgery will evaluate by watching videos independently. If the surgical condition suddenly worsens, additional assessments will be performed.

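### Duration of surgery is compared by an unadjusted two-sample test, although a surgeon- and procedure-specific expected duration must be determined for every patient before randomization

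*Protocol article*

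**What the plan says.** The statistical analysis section sends the four repeatedly measured outcomes (cystatin C, creatinine, surgical rating, renal oxygen saturation) to a model: "the effect of intervention in the whole timeframe will be analyzed by a mixed-effects model". For everything else on a continuous scale it states "Other continuous variables will be compared by two-sided independent Student" t tests or the Mann–Whitney U test. In Table 3 the continuous outcomes without repeated measurement are duration of surgery (surgical condition domain) and intraoperative urine output (renal function domain). Both have a mean difference between groups as the effect measure.

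Under Participant selection, eligibility depends on an expected duration above 3 hours, and that value is "determined by the average duration of the same type of surgery by the same surgeon in the last year". Randomization comes later: "After enrollment, just prior to the surgery, the patients will be randomized". The sequence is described as "The allocation sequence will be computer-generated using random block sizes", and no stratification by surgeon or procedure is stated. Under Surgical condition rating, the article says "The laparoscopic pelvic surgeries for the enrolled patients will be performed by five surgeons".

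The only covariate rule is conditional: "Unbalanced variables at baseline will be included in the ANOVA or mixed-effects model to adjust for the potential confounding effect". A standardized difference below 0.2 counts as balanced. The baseline items listed under Data collection do not include surgeon, procedure or expected duration. Table 1, which marks the baseline variables, is not reproduced in the text at hand.

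**The concern.** The eligibility rule itself treats surgeon and type of operation as predictors of how long a case will take. The resulting value exists before allocation, so it cannot be affected by treatment and is a proper baseline covariate. The stated test discards it, and differences between surgeons and between procedures stay in the error term.

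Duration is not a trivial outcome here. The Background gives longer surgery as a known drawback of low pressure, and better surgical conditions under deep block are a stated objective. Duration is one of only three outcomes that address it. An interval wider than necessary makes a null result on duration harder to read, whether the question is about pressure or about depth of block.

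**Working it through.** **1. The plan's own figure.** The article gives no power or precision target for duration. Its one sample size is for cystatin C: SD 0.186, difference 0.05, two-sided 5%, power 90%. Per factor level, n = 2 × (1.960 + 1.2816)² × 0.186² / 0.05² = 290.8, so 291 and 582 in total, as stated. Then 582 / 0.90 = 646.7, rounded up to 648 for four equal groups (162 per group, 324 per factor level). These figures reproduce, and nothing below touches them.

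**2. What adjustment is worth.** Let R² be the share of the variance in actual duration explained by surgeon and expected duration. The documents give no R², so it is an assumption shown over a range. The standard error is multiplied by √(1 − R²), and the effective sample size by 1 / (1 − R²). With 291 per factor level, the difference detectable at 90% power is 3.2415 × √(2/291) × √(1 − R²) in SD units. The power column assumes a true difference of 0.2 SD.

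| R² (assumed) | SE multiplier | Fall in SE | Effective n multiplier | Detectable difference (SD) | Power at 0.2 SD |
|---|---|---|---|---|---|
| 0 (as planned) | 1.000 | – | 1.00 | 0.269 | 67.5% |
| 0.1 | 0.949 | 5% | 1.11 | 0.255 | 72.0% |
| 0.3 | 0.837 | 16% | 1.43 | 0.225 | 82.2% |
| 0.5 | 0.707 | 29% | 2.00 | 0.190 | 92.7% |

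**3. Simulation check.** Trials of 582 patients with normal data were simulated 4000 times per setting. For a true difference of 0.2 SD, power was 0.68 (t test) against 0.83 (adjusted) at R² = 0.3, and 0.67 against 0.93 at R² = 0.5. With no true difference, the t test rejected in 0.059 and 0.049 of runs and the adjusted analysis in 0.050 at both. The t test is exact under this model, so the 0.059 is simulation noise. The unadjusted test holds its level.

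**4. Whether the imbalance rule already covers this.** Suppose expected duration were recorded as a baseline variable. Comparing factor levels of 324, the chance standardized difference has SE √(2/324) = 0.079. The threshold is 0.2 / 0.079 = 2.55 SEs away, a two-sided probability of about 1%. If balance were instead checked between single groups of 162, the SE is √(2/162) = 0.111, the threshold is 1.80 SEs away, and any one pair exceeds it about 7% of the time. For at least one of the six pairs, the range of four means gives about 27% (studentized range 0.2 × √162 = 2.55). The rule is therefore rare in the main-effect comparisons and less rare if it runs over all four groups. Either way it depends on the data, and it leads to an ANOVA or mixed model, not to the test stated for duration.

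**5. What the rule leaves in.** An imbalance of 0.19 SD in the covariate would be tolerated. It moves the unadjusted estimate by 0.19 × √R². At R² = 0.3 that is 0.10 SD, or 1.3 unadjusted SEs (0.104 / 0.0786). At R² = 0.5 it is 0.13 SD, or 1.7 SEs (0.134 / 0.0786). This is part of the random error that the unadjusted SE already counts. Adjustment removes it.

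**The case against.** Nothing here is invalid. Under randomization the unadjusted difference is unbiased, its level is right, and its standard error already allows for chance imbalance. This stands in full: the loss is one of precision.

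Every R² above is assumed. Because only cases expected to last more than 3 hours are eligible, the covariate is truncated, which may lower its R². This also stands. At 10% the gain is modest, about 4.5 percentage points of power at 0.2 SD.

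The article foresees adjustment, and since repeated outcomes go to the mixed model, its mention of ANOVA may be meant for outcomes such as duration. That reading is fair, but it conflicts with the test actually named, and the trigger remains observed imbalance. Table 1 may list surgeon or procedure as baseline variables. A t test or Mann–Whitney U test would still not use them.

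Covariates for secondary outcomes are often left to the analysis plan. That would answer a complaint about silence, but here the article names a test that admits no covariate.

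Three stronger readings are tempting and not supported:

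- **Surgical ratings.** A reader might infer that they too are analysed without surgeon or procedure. They go to a mixed-effects model whose terms are not listed, so the text neither includes nor excludes such terms.
- **Urine output.** It gets the same test, but it is a renal outcome, and the documents show no link between it and expected duration.
- **Primary and other renal models.** No figure in the documents supports a gain from adding these covariates there.

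**Conclusion.** The point holds for duration of surgery, as avoidable loss of precision on one secondary outcome. The article fixes a test without covariates while its own eligibility rule produces a baseline predictor of that outcome for every patient. The standard error could fall by about 5%, 16% or 29% at an assumed R² of 0.1, 0.3 or 0.5, equivalent to 11%, 43% or 100% more patients for that comparison. The size rests on the assumed R²; the direction rests on surgeon and procedure predicting duration at all, which the eligibility rule presupposes. A reader might go further and infer bias, inflated type I error or a flawed sample size. The documents support none of these: the stated test is valid, and 582 and 648 reproduce.

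**What to change.** State in advance that duration of surgery will be analysed by a linear model containing both randomized factors (pressure and depth of block), surgeon (five levels) and the expected duration determined at screening. Report the adjusted mean difference, so that the effect measure in Table 3 is kept; a log transformation would change it. Include the covariates whatever the observed balance. The same model may be used for intraoperative urine output, where the gain is less certain.

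The cost is a change of analysis wording and two more items in the case report form: the surgeon and the expected duration. The second must be carried over deliberately, because the screening investigator takes no part in data collection and the listed baseline data do not include it. No additional patients or measurements are needed.
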